### Outcomes

The primary outcomes will be maternal morbidity during pregnancy and delivery reported by women after their latest completed pregnancy (from pregnant women delivering in wards receiving home visits, and from women reporting on their latest completed pregnancy at the baseline visit in the wards not yet receiving the home visits). We will measure rates of severe headaches, swelling of hands and feet, blurred vision, high blood pressure (if measured), problems with urine (if tested), convulsions, and vaginal bleeding during pregnancy. We will also measure rates of reported post-partum high fever and smelly discharge. The study is not powered to detect a difference in maternal mortality between the intervention and control wards but we will nevertheless record and compare maternal deaths between intervention and control wards. Primary outcomes for infants will be pregnancy outcomes (livebirth, stillbirth, miscarriage), birthweight (in terms of the baby being reported as big, normal, or small), immunisation history, and history of episodes of diarrhoea.

Secondary outcomes will be variables in the CASCADA sequence measured in both women and their male partners, including: conscious knowledge about danger signs in pregnancy and about factors related to complications during pregnancy and delivery, attitudes about care for women during pregnancy and delivery, subjective norms about pregnancy and willingness to deviate from unhelpful norms, intention to change behaviours to protect the health of pregnant women, perceived agency to make changes, discussion about pregnancy and delivery between husband and wife, and actual changes in practices reported (particularly in relation to domestic violence and heavy work in pregnancy). We will also analyse any differences in access to health services between pregnant women in intervention and control wards: the proportions who had antenatal care visits to facilities, who had their blood pressure measured, who had their urine tested, who delivered with a skilled attendant, and who delivered in health facilities.

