### The intervention

Each team of one trained female and one trained male home visitor will have a catchment area of around 300 households, and will visit every household every two months. On the first visit the female visitor will ask about household demographics and socio-economic status. On each subsequent visit, she will check how many women of child bearing age (14–49 years old) are in the household. She will ask each woman of child bearing age about her last pregnancy using the pregnancy history questionnaire. For each currently pregnant woman she will administer a pregnancy surveillance questionnaire. This surveillance questionnaire will be repeated on each two-monthly visit, so a woman contacted early in pregnancy could complete four surveillance questionnaires during her pregnancy. A questionnaire after delivery will record information about the whole pregnancy and delivery, about any maternal deaths, and about birth weight and any neonatal deaths. A final visit one year later will record infant outcomes, including immunisation and episodes of diarrhoea. Male visitors will interview the male partners of the pregnant women, also every two months. The male visitors will not necessarily visit at the same time as the female visitors; many will visit in the evenings or at weekends, when they are more likely to find the male partners at home.

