### Data collection and analysis

The unit of randomization, intervention and analysis will be the ward. Information on outcomes (maternal morbidity, pregnancy behaviours and care, intermediate CASCADA variables) will come from the questionnaires about last completed pregnancies: from pregnant women delivering in wards receiving home visits, and from women reporting on their latest completed pregnancy at the baseline visit in the wards not yet receiving the home visits. The home visitors will also record maternal deaths.

To measure the impact of home visits compared with no home visits, we will contrast outcomes in wards receiving visits and those not yet receiving visits (wave 1 vs wave 2 in second year; wave 2 vs wave 3 in third year). The first round of home visits in wave 2 and wave 3 will provide the data for these waves as “controls” for the already visited waves (Fig. 2). To assess the impact of the added edutainment in the home visits, we will compare outcomes between the ward with basic visits and the ward with edutainment visits, within each wave. In total, we will compare 3 wards without edutainment with 3 wards with edutainment. We will use generalised estimating equations to incorporate the cluster design and differences at baseline, assuming an exchangeable correlation structure within wards [49].

In addition to the comparisons of proportions of outcomes between visited/not-visited wards and between video/non-video in visited wards, we will also undertake a more detailed analysis of intermediate outcomes in the CASCADA chain. We have previously done this in a cluster randomized controlled trial of community mobilisation for dengue prevention in Mexico [44]. This CASCADA analysis involves transitive closure treating the partial order as a bipolar weighted diagraph [50] with directed edges (arcs) from each factor to each later factor in the order. We convert these to input matrices by rescaling odds ratios from − 1 to 1, using the formula 1-(2/(OR + 1)) and submit these to fuzzy transitive closure using the ProbClosure package [51].

We will estimate the coverage of the home visits program in each ward by comparing the numbers in the submitted data with the population projections from the 2006 census, updated in the baseline household mapping exercise in each ward. We will also measure the proportions of pregnant women who received different numbers of the two-monthly follow up home visits.

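### The pregnancies that supply the primary maternal outcomes are defined differently in visited and control wards, and miscarriage, itself a primary outcome, has no stated source by arm

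*Protocol article*

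**What the plan says.** The Outcomes section introduces the primary maternal outcome as "maternal morbidity during pregnancy and delivery reported by women after their latest completed pregnancy". A parenthesis then splits the source by arm: "from pregnant women delivering in wards receiving home visits, and from women reporting on their latest completed pregnancy at the baseline visit", the second group being the wards still waiting for visits. Data collection and analysis repeats the split. Outcome information "will come from the questionnaires about last completed pregnancies: from pregnant women delivering in wards receiving home visits" for the visited wards, and for the others from women describing their latest completed pregnancy at the first visit. The outcomes listed there are "Information on outcomes (maternal morbidity, pregnancy behaviours and care, intermediate CASCADA variables"; pregnancy outcomes such as miscarriage are not in that list.

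For infants, the Outcomes section states: "Primary outcomes for infants will be pregnancy outcomes (livebirth, stillbirth, miscarriage", followed by reported birth size, immunisation and diarrhoea. It gives no source by arm for these.

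The Intervention section describes the forms used in visited wards. "For each currently pregnant woman she will administer a pregnancy surveillance questionnaire", repeated every two months. When the pregnancy is over, "A questionnaire after delivery will record information about the whole pregnancy and delivery, about any maternal deaths, and about birth weight and any neonatal deaths"; miscarriage is not named. The same section also has the visitor put a pregnancy history questionnaire about the last pregnancy to each woman of child-bearing age.

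**The concern.** A miscarriage is a completed pregnancy, but in ordinary use a woman who miscarries has not delivered. Taken at its word, the rule lets a control woman whose latest pregnancy miscarried into the denominator and keeps her visited counterpart out. Even if *delivering* is read loosely as completing a pregnancy, the visited group consists of women found pregnant at a two-monthly round. A pregnancy lost before the visitor finds it does not reach that group.

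The two arms would then differ in which pregnancies are eligible, whatever the visits do. Perfect recall, identical calendar periods and the planned generalised estimating equations would not remove this. At stake are the primary maternal morbidity comparisons, and whether miscarriage, a primary outcome, can be compared between arms at all.

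**Working it through.** The article states no figure on this point, so there is nothing of its own to reproduce. The check reads the definitions side by side and then sizes the effect under stated assumptions.

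**Definitions**

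| | Visited wards | Control wards |
|---|---|---|
| Maternal outcomes | pregnant women who deliver | latest completed pregnancy, recalled at the first visit |
| Can a miscarriage enter? | no, or less often | yes, if it is the latest pregnancy |
| Source for miscarriage as an outcome | not stated | not stated |

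**Inputs**
- Complication rate 58% and target reduction 20%, from Sample size. The 58% is taken here as the rate among pregnancies ending in birth. The visited rate is then 0.80 × 0.58 = 0.464.
- f, the share of control latest completed pregnancies that are miscarriages. Not in the article; assumed 5% to 15%.
- q, the complication rate among those miscarriages. Not in the article; varied from 0 to 1.
- No miscarriages in the visited denominator (the literal reading).

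**Formulas**

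Control rate = 0.58 × (1 − f) + q × f

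Apparent risk ratio = 0.464 / control rate

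| f | q = 0 | q = 0.29 | q = 0.58 | q = 1 |
|---|---|---|---|---|
| 5% | 0.464/0.551 = 0.842 | 0.464/0.5655 = 0.821 | 0.800 | 0.464/0.601 = 0.772 |
| 10% | 0.464/0.522 = 0.889 | 0.464/0.551 = 0.842 | 0.800 | 0.464/0.622 = 0.746 |
| 15% | 0.464/0.493 = 0.941 | 0.464/0.5365 = 0.865 | 0.800 | 0.464/0.643 = 0.722 |

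With q between zero and half of 58%, the true 0.80 appears as 0.82 to 0.94. At q = 0.58 there is no bias. Above that the apparent ratio falls below 0.80 and flatters the visits.

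**By symptom.** Dividing through by 0.58 gives apparent ratio = 0.80 / [(1 − f) + f × r], where r is the symptom rate in miscarriages relative to births. Only f and r matter, not the base rate.
- Post-partum fever and discharge: if miscarriages are counted as free of these, r = 0. The ratio is 0.80/0.95 = 0.842 to 0.80/0.85 = 0.941, so a benefit is understated.
- Vaginal bleeding in pregnancy: r may well exceed 1, in which case a benefit is overstated.

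**Partial capture.** If the visited denominator includes some miscarriages, the bias shrinks. With 10% in control, 5% in visited and r = 0, the ratio is 0.80 × 0.95/0.90 = 0.844, against 0.889 with none. It vanishes when the two shares are equal.

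**The case against.** Both sections place the two arms under one umbrella, the last or latest completed pregnancy, so *delivering* may be loose wording. That is possible. But the text then specifies each arm differently, in two places, and the loose reading still leaves out losses before a woman is found pregnant. The wording needs correcting on either reading.

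A reader might infer that miscarriage is bound to be undercounted in visited wards, with a rate near zero. The documents do not support that. The source rule is attached to maternal and intermediate outcomes, not explicitly to miscarriage. The pregnancy history questionnaire could record losses in visited wards, although the article does not make clear how often it is asked or whether it feeds this analysis. Two-monthly surveillance may pick up losses that one-off recall misses. In control wards, asking only about the latest completed pregnancy drops any miscarriage followed by another completed pregnancy. Losses before registration push the other way. The net direction is open.

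A reader might also infer that morbidity is always biased against the visits. That requires miscarriages to carry less morbidity than births, which is doubtful for bleeding.

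The denominator behind the 58% is not shown and may already include miscarriages. This affects the illustrated control rates, but not the ratios expressed through f and r.

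Finally, this is a condensed article, and the questionnaires may settle how losses are recorded. That would answer the gap on miscarriage. It would not undo a source rule for morbidity that the article states and repeats.

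**Conclusion.** The concern holds for maternal morbidity. The article fixes a different set of eligible pregnancies in each arm, and pregnancies ending in miscarriage can enter the control denominator but not, or less often, the visited one. The bias runs in different directions by symptom: control rates of post-partum fever and discharge are lowered, and control rates of vaginal bleeding may be raised. On the assumptions above, a true risk ratio of 0.80 would appear as about 0.82–0.94 if miscarriages carry zero to half the 58% morbidity, and below 0.80 if they carry more than 58%. Those figures rest on an assumed 5–15% share and on no miscarriages in the visited denominator. They illustrate the possible size and are not estimates from trial data.

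For miscarriage as an outcome the conclusion is narrower. It is primary, it has no stated source by arm, and the only end-of-pregnancy form described for visited wards follows delivery. Comparability is therefore not assured, but an undercount in visited wards is not established.

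**What to change.** In Outcomes and in Data collection and analysis, state one eligibility rule for both arms: maternal morbidity and birth outcomes are analysed among pregnancies that ended in live birth or stillbirth, identified from the recorded pregnancy outcome. No gestation cut-off is needed, and the article does not show that gestation at the end of pregnancy is collected.

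Take miscarriage in both arms from the same instrument, the pregnancy history questionnaire described under The intervention, and state when it is asked in visited wards. Otherwise, do not treat miscarriage as a primary between-arm comparison.

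The cost is a change of wording and a filter on recorded pregnancy outcome. The control denominator becomes slightly smaller, and miscarriage may lose primary status. Two limits should be acknowledged. The line between miscarriage and stillbirth will rest on what is reported, so the categories must be the same on both forms. Restricting to births also conditions on an event that the visits could influence, and leaves bleeding in pregnancies that miscarried outside the morbidity comparison.

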### Timeline

Figure 2 depicts the timelines of the study. At the beginning of the study, we will randomly allocate the six participating wards in Toro LGA into three waves of two wards each. All households in the wave one wards will start to receive home visits immediately. Households in wave two wards will start to receive home visits about one year later, and households in wave three wards will start to receive visits after a further year. By the end of the study period, households in all six wards will be receiving visits. In three of these wards, the visits will include using the video edutainment, while in the other three wards the visits will convey information without the assistance of the video clips.

### Sample size

Our sample size calculations use the clinical trials simulator of Taylor and Bosch [48]. Maternal morbidity and intermediate outcomes in the CASCADA model are common so the study will have power to detect quite small shifts in these outcomes. Our 2013 study found 60% of Toro women did not reduce heavy work in pregnancy and 58% had evidence of post-partum infection or another serious complication of pregnancy [32]. At this level of occurrence, based on an estimated 2880 births in each ward over a two year period, our study will be able to detect a 20% reduction in complications (80% power at the 5% level, k = 0.05) between the home visit wave 1 wards and the next two wards before they start visits (wave 2).

Assuming the visits do reduce post-partum infection by 20%, a comparison of the three wards with visits plus edutainment versus the three with basic home visits would be able to detect a further improvement of 15% (80% power at 5% level, k = 0.05).

The study is not powered to show an impact on maternal mortality, although this should be measurable with later rollout to other LGAs. The Toro MMR of around 800 per 100,000 live births implies around 35 maternal deaths in each ward over a two year period. The wards with universal home visits would have to reduce mortality by 35% to be detected with 80% power at the 5% level (k = 0.06). Assuming the universal home visits reduced mortality risk by this amount, the video edutainment would need to reduce this by a further 60% for this to be detected across three dyads with 80% power at the 5% level.

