### Trial design

This is a pragmatic cluster randomized controlled trial (CRCT) in a stepped-wedge design [45, 46], anticipating further rollout after the project and in the meantime allowing us to compare maternal outcomes between wards randomly allocated to receive home visits early with those allocated to receive home visits after a delay (control wards). The two wards in wave 1 will be compared with the two wards in wave 2, and wave 2 wards will be compared with wave 3 wards.

Among wards receiving home visits, one half will be randomly allocated to receive basic home visits and the other half to receive visits plus edutainment (presentation and discussion of evidence-based video clips). We will therefore be able compare maternal outcomes between wards receiving home visits with and without the edutainment element.

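### The 80% power stated for wave 1 against wave 2 rests on an approximation that is too generous at two wards per arm; a two-sided ward-level t-test on the same inputs has about 56–59%

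*Protocol article*

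**What the plan says.** The Sample size section of the protocol article takes as its base rate that "58% had evidence of post-partum infection or another serious complication of pregnancy". It states its result "based on an estimated 2880 births in each ward over a two year period", and the result is: "our study will be able to detect a 20% reduction in complications (80% power at the 5% level, k = 0.05". The comparison being powered is "between the home visit wave 1 wards and the next two wards before they start visits (wave 2". The Trial design section confirms its size: "The two wards in wave 1 will be compared with the two wards in wave 2". The same Sample size paragraph describes these outcomes as common, "so the study will have power to detect quite small shifts in these outcomes".

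Two other places bear on the figure. Data collection and analysis makes the ward the unit of randomisation, intervention and analysis, and names generalised estimating equations (GEE) with exchangeable correlation within wards. Timeline says "Households in wave two wards will start to receive home visits about one year later", and the abstract puts the wave 1 against wave 2 comparison at about one year.

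**The concern.** With the ward as the unit of analysis, this comparison has four independent units. Between-ward variation then has to be estimated from two wards in each arm, which leaves 2 degrees of freedom and a two-sided 5% critical value of 4.30 rather than 1.96. Thousands of births per ward do little to help, because they do not add wards. A claim of 80% power at that size needs a calculation that allows for so few clusters. The birth count also covers two years, although wave 2 starts visits about one year after wave 1.

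Interpretation is at stake. If readers believe that the study had 80% power for a 20% reduction and could see small shifts, they will take a null home-visit result as evidence against an effect. On the plan's own inputs, a valid two-sided test would miss a true 20% reduction about four times in ten.

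**Working it through.** **Inputs.** From the Sample size section: p0 = 0.58; a 20% reduction, read as relative, so p1 = 0.58 × 0.80 = 0.464 and d = 0.116; k = 0.05; 5% level; m = 2880 births per ward over two years, so 1440 per year. From Trial design: c = 2 wards per arm. Assumed because not stated: k is the between-ward coefficient of variation, the test is two-sided, and wards are of equal size. Reading k as an intra-cluster correlation instead gives only about 18% power even with a normal test, so that reading cannot be what was meant.

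**Variance.** V = p0(1−p0)/m + p1(1−p1)/m + k²(p0² + p1²)

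- m = 2880: 0.2436/2880 + 0.2487/2880 + 0.0025 × (0.3364 + 0.2153) = 0.00155
- m = 1440: 0.2436/1440 + 0.2487/1440 + 0.00138 = 0.00172

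**Step 1: reproduce the plan's figure.** Wards per arm c = 1 + (1.96 + 0.84)² × V/d², with (1.96 + 0.84)² = 7.849 before rounding and d² = 0.01346.

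- m = 2880: 1 + 7.849 × 0.00155/0.01346 = 1.90, rounded up to 2. Power with c = 2 is Φ(0.116/√0.00155 − 1.96) = Φ(0.986) = 83.8%.
- m = 1440: 1 + 7.849 × 0.00172/0.01346 = 2.00. Power is Φ(2.796 − 1.96) = 79.8%.

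The same formula gives detectable edutainment effects of 14.2% (2880 births) and 15.2% (1440) for three wards against three, in line with the stated 15%. This is very probably how the figures arose.

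**Step 2: two-sided t-test on ward proportions, 2 df.** SE = √(V/2), δ = d/SE, and power is the probability that a non-central t with 2 df and non-centrality δ exceeds 4.303.

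| Births per ward | SE | δ | Power |
|---|---|---|---|
| 2880 | 0.0278 | 4.17 | 59% |
| 1440 | 0.0293 | 3.95 | 56% |

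Beta-binomial simulation gave 59.8% and 55.9%, and the test kept its 5% level.

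If only wave 1 is limited to one year of births, V = 0.000926 + 0.000711 = 0.00164, δ = 4.06, and power is about 57%.

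**Step 3: other tests on the same four wards (2880 / 1440 births).**

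| Test | Power | Type I error |
|---|---|---|
| Normal test, no added ward | 98.6% / 97.7% | between-ward variance treated as known |
| GEE-type sandwich test, normal critical value | about 99% / 99% | about 30% |
| GEE-type sandwich test, t critical value on 2 df | 81% / 77% | about 9% |
| Unpaired t, 2 df, two-sided | 59% / 56% | 5% (simulated) |
| Unpaired t, 2 df, one-sided | 82.7% / 79.6% | needs a one-sided 5% test |
| Paired t, 1 df, two-sided, no gain from pairing | 25.6% / 24.4% | nominal 5% |

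**Step 4: what 80% power would need on 2 df.** At k = 0.05 the detectable reduction is between 26% and 27% at 2880 births (79.0% and 81.6% power) and about 28% at 1440 (80.7%). For the planned 20% reduction, k would have to be about 0.035 (2880 births) or 0.03 (1440). At an assumed k = 0.10 and 1440 births, power for a 20% reduction is 24%, and the detectable reduction is about 47%.

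**The case against.** The strongest reply is that the plan's number is reproducible. A recognised cluster formula returns it from the stated inputs, and still returns it with half the births. That stands: a reader might infer an arithmetic error, and there is none. The defect is the choice of approximation for two wards per arm.

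A second reply is that the plan names GEE and not a t-test, that it does not state sidedness, and that a small-sample correction may be left to the statistical analysis plan. It is true that the article does not prescribe a 2-df test, so 56–59% depends on that choice. But the ward is declared the unit of analysis, and none of the two-sided tests examined reached 80% at k = 0.05 while holding the 5% level. GEE without correction gets there only by inflating the error rate. A one-sided test would match 80%, but the article does not say that one is intended.

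A third reply is that the birth window hardly matters. In size this is right, at about 3.5 points. A reader might also infer that control numbers are capped at 1440 per ward. The documents do not support that: control data are latest completed pregnancies reported at the baseline visit, with no stated look-back limit, and earlier pregnancies were unvisited too. The one-year limit applies more clearly to wave 1 deliveries under visits. Even there, Data collection and analysis speaks of the second year while the abstract says about one year.

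Finally, the trial also plans a wave 2 against wave 3 comparison. That adds information, but it is not the comparison to which the 80% is attached.

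**Conclusion.** The concern holds in a limited form. On the plan's own inputs, power for a 20% reduction between two and two wards is about 56–59% with a two-sided ward-level t-test, against the stated 80%. The statement about small shifts is not supported, since about a 28% relative reduction is needed for 80% power at k = 0.05 and 1440 births. This rests on k being a coefficient of variation, a relative reduction, a two-sided 5% test, equal ward sizes and no gain from pairing.

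Several stronger conclusions are tempting but unsupported:

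- **That k is really larger.** The contrast between Toro (60%) and the state (82%) in not reducing heavy work compares a local government area with the whole state. It says nothing about ward-to-ward variation within Toro, so results at k = 0.10 are a sensitivity analysis only.
- **That early births dilute the effect by a known amount.** The document gives no exposure pattern from which to calculate this, and the 20% can be read as the average effect in the births analysed.
- **That the edutainment claim fails equally.** Three wards against three on 4 df gives about 78% at 2880 births, close to what is stated.

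**What to change.** In the Sample size section:

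1. Recalculate the wave 1 against wave 2 power with a small-sample, t-based method, and state the test, its sidedness and the meaning of k.
2. Use a birth window that matches the comparison, stated separately for wave 1 deliveries and for retrospective control pregnancies.
3. Report the result: about 56% power for a 20% reduction, or a detectable reduction of about 28% at 80% power (k = 0.05, 1440 births per ward).
4. Show sensitivity to k, labelled as an assumption; for example, about 47% detectable at k = 0.10.
5. Delete the clause about small shifts.

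This takes a recalculation and some text. It needs no extra participants and no change of design, and the planned wave-by-wave comparisons can stay as they are; a pooled six-ward power figure is not required. The price is a less favourable stated figure.

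### The expected maternal deaths per ward do not follow from the protocol's own births and mortality ratio (23, not 35), and the planned visited versus not-visited contrasts do not give 80% power for a 35% mortality reduction

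*Protocol article*

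**What the plan says.** All the figures at issue stand in the Sample size section of the protocol. For morbidity, the calculation is "based on an estimated 2880 births in each ward over a two year period". For mortality, the section says: "The Toro MMR of around 800 per 100,000 live births implies around 35 maternal deaths in each ward over a two year period". It continues: "The wards with universal home visits would have to reduce mortality by 35% to be detected with 80% power at the 5% level", with k = 0.06. A further reduction of 60% is then given for video edutainment across three pairs of wards, on the assumption that the 35% reduction has been achieved.

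The section does not define k, say whether the test is one- or two-sided, or give the number of wards per arm behind the 35%. The calculations used a trial simulator that the protocol cites.

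On the design, the Timeline section says: "we will randomly allocate the six participating wards in Toro LGA into three waves of two wards each", with waves starting about one year apart. The Data collection and analysis section sets the visited versus not-visited contrasts as "wave 1 vs wave 2 in second year; wave 2 vs wave 3 in third year". Each contrast is therefore two wards against two.

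Both the Outcomes section and the Sample size section say that the study is not powered for maternal mortality. The Outcomes section adds that deaths will still be recorded and compared.

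**The concern.** The birth count and the death count share the same unit (one ward) and the same period (two years), and the death count is presented as following from the mortality ratio. The three figures must therefore agree, and they do not.

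The detectable reduction depends on the number of deaths and the number of wards. If the deaths are overstated, or if the 35% assumes more wards than a contrast contains, the sentence gives too favourable a picture of the planned mortality comparison. The edutainment figure inherits the problem because it starts from the 35%.

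No primary outcome or design decision hangs on these figures. What is at stake is the accuracy of a published event count and power statement.

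**Working it through.** **1. Expected deaths.** Inputs from the Sample size section: 2880 births per ward over two years; 800 deaths per 100,000 live births, i.e. 0.008; stated result about 35.

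- 2880 × 0.008 = 23.04, so the stated figure is not reproduced. 35 / 23.04 = 1.52.
- 35 deaths at this ratio need 35 / 0.008 = 4,375 births per ward.
- 35 deaths from 2880 births need a ratio of 35 / 2880, about 1,215 per 100,000.
- Three years of births at the same rate give 4,320 × 0.008 = 34.6. That is one possible origin of the figure, but the text says two years.
- The ratio is per live birth, so any births among the 2880 that were not live would bring the count below 23.

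**2. Power for a 35% reduction.** The cited simulator was not available, so I used the standard closed form for unmatched clusters. Assumptions: k = 0.06 is the between-ward coefficient of variation, and the test is two-sided at 5%.

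With p0 = 0.008, p1 = 0.65 × 0.008 = 0.0052, n births per ward and c wards (or ward-periods) per arm:

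variance of the difference = [p0(1 − p0)/n + p1(1 − p1)/n + k²(p0² + p1²)] / c

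For n = 2880 the bracket is 2.756 × 10⁻⁶ + 1.796 × 10⁻⁶ + 0.328 × 10⁻⁶ = 4.879 × 10⁻⁶. The difference is 0.0028.

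- c = 2: SE = √(4.879 × 10⁻⁶ / 2) = 0.001562; 0.0028 / SE = 1.79.
- c = 4: SE = 0.001104; 0.0028 / SE = 2.54.

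Normal power is Φ(ratio − 1.96). The t version uses a noncentral t with 2(c − 1) degrees of freedom.

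| Births per ward | Deaths per ward without visits | Wards or ward-periods per arm | Power, normal | Power, t |
|---|---|---|---|---|
| 2880 | 23 | 2 v 2 | 43% | 19% |
| 2880 | 23 | 3 v 3 | 59% | 39% |
| 2880 | 23 | 4 v 4 (both contrasts pooled) | 72% | 57% |
| 2880 | 23 | 6 v 6 | 87% | 80% |
| 1440 (one year, births spread evenly) | 11.5 | 2 v 2 | 25% | 12% |
| 1440 | 11.5 | 4 v 4 | 45% | 34% |
| 4320 | 34.6 | 2 v 2 | 58% | 24% |
| 4320 | 34.6 | 4 v 4 | 86% | 72% |

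The pooled rows count wave 2 wards once on each side and treat the ward-periods as independent, which is generous.

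Clustering is not the main obstacle. Ignoring it, 0.80% against 0.52% needs 13,127 births per arm, which is 13,127 / 2880 = 4.6 wards. A two-ward arm has 5,760 births.

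**3. Detectable reduction at 80% power** (normal to t):

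- 2880 births: about 38% to 45% for pooled 4 v 4; about 52% to 90% for 2 v 2.
- 1440 births: about 51% to 60% for pooled 4 v 4; 68% by the normal approximation for 2 v 2, and no reduction below 100% reaches 80% on 2 degrees of freedom.

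**4. Where the 35% might come from.** It is matched by 23 deaths with six wards per arm (t power 79.9%), or by 35 deaths with three wards per arm and no clustering (80%). Neither is a planned visited versus not-visited contrast.

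**5. Edutainment figure.** From a base of 0.0052 with 2880 births per ward, 3 v 3 and k = 0.06 (no k is given for this figure), the detectable further reduction is about 52% (normal) to 66% (t). The stated 60% lies inside that range, so it is not shown to be wrong. It does rest on the 35% base.

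**The case against.** The strongest reply is that the protocol disclaims mortality power twice, so the 35% illustrates why mortality is out of reach and is not a design target. That stands, and it limits the importance of the point. It does not make 23 into 35, and it does not justify an 80% power statement that the planned contrasts do not support.

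A second reply is that the ward count, the meaning of k and the sidedness are unstated and the simulator cannot be seen, so the 35% might be right under some reading. This stands in part. With a one-sided 5% test and pooled 4 v 4 at 2880 births per ward-period, normal power is 81%. That reading needs a one-sided test the document does not state and two full years of births in every ward-period, although waves start about a year apart. At 1440 births it falls to 57%.

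A reader might make three stronger inferences that the document does not support:

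- **The 35% fails even with 35 deaths per ward.** It fails for 2 v 2, but pooled 4 v 4 gives 86% (normal) or 72% (t), so failure is not established there.
- **The remark that an effect should be measurable with later rollout rests on these figures.** That remark comes before them in the paragraph, and it rests as naturally on adding more local government areas.
- **52% or 90% should replace the 35%.** Those values assume a single 2 v 2 contrast with two full years of births, which is only one of several possible readings.

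**Conclusion.** The death count is wrong on the protocol's own inputs: about 23 per ward over two years, not 35, an overstatement of about 52%. This needs no assumption beyond the three figures printed in the section.

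The power statement is not met by the planned visited versus not-visited comparisons at 23 deaths per ward. Even the generous pooled reading reaches only 72% (normal) or 57% (t). This part assumes that k is the between-ward coefficient of variation, a two-sided 5% test, closed-form variance in place of the cited simulator, and 2880 births in each ward-period. Shorter exposure makes it worse.

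Severity is low. Mortality power is already disclaimed, and the sample size does not depend on these figures.

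**What to change.** - Change the deaths to about 23 per ward over two years. If 35 was intended, reconcile births, period and mortality ratio so that they produce it.
- Rerun the detectable mortality reduction for the contrast that will actually be made. State wards per arm, births per ward-period, the definition of k and the sidedness. As a guide, the closed form with 2880 births gives about 38% to 45% for pooled 4 v 4 and about 52% to 90% for 2 v 2, and larger values with one-year exposure. The authors' own rerun should supply the printed figure.
- Recompute the conditional 60% edutainment figure from the corrected base.

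The cost is a text correction and one rerun of an existing calculation. Design, data collection and primary analysis are unaffected.
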